### Ethical considerations

All participants will receive information about the study and have opportunity to ask questions. Written informed consent will be obtained from participants after they receive comprehensive details on (i) the purposes of the study; (ii) the allocation process; (iii) the use of data and the means of assuring confidentiality; (iv) voluntary participation and the participant’s right to withdraw from the study at any time and (v) any potential harm that could occur because of the intervention. Consent will be acquired prior to obtaining any study measurements. The study protocol was developed using the Standard Protocol Items: Recommendations for Interventional Trials (SPIRIT) Checklist (see Additional file 1) and adheres to the SPIRIT recommendations. The trial is registered with ClinicalTrials.gov as NCT03438370 and has received ethical clearance from the Lesotho National Health Research Ethics based at the Ministry of Health as well as Chesapeake Institutional Review Board in the USA [Number: ID49–2017 and MOD00231007 respectively].

## Discussion

In this paper, we present and describe a demonstration study protocol that will evaluate retention in care, virologic suppression, feasibility and cost effectiveness of community based differentiated models of MMD approaches of ART among stable HIV patients in Lesotho. Community based models for delivering ART have potential of being an integral part of strengthening the HIV treatment cascade. To meet the UNAIDS targets to end the AIDS epidemic by 2030, a need exists in diversifying ART delivery in ways that are acceptable to communities and maintaining good outcomes including retention and viral suppression [4, 10]. However, community systems must be adequately resourced, including infrastructure that allows for linking and integration with health facilities, allowing for better sustainability and scaling -up.

The WHO has recommended provision of ART through community models, only if operating guidance and monitoring are provided [5]. These strategies are to ultimately significantly reduce the burden experienced by patients and health care providers. Though all models, are to include stable patients, in this context virologically suppressed, and those who are able to adhere to ART [11], the community multi month dispensing approaches including both CAGs and community ART distribution points have been shown and postulated to provide gains for patients by (i) reducing time and transport costs (WHO, 2016), (ii) increasing peer support for adherence (through clubs and CAGs) [11, 12] (iii) reduced defaulting and enhancing community participation [5]. Whereas, for health providers it (i) reduces workload (ii) and maintains and improves health outcomes and improves self-management of patients. Additionally, these approaches, could be extended to key populations including migrants in Sub Saharan Africa, where patients move away from their homes for work and other economic reasons [13]. A study among migrants, assessing healthcare needs, preferences and accessibility barriers of HIV-positive migrant patient populations in high disease burden, borderland districts of Lesotho showed that less than 7% opted for a 1–2 month ARVs refills [14]. Whereas 30.2%and 63% indicated a preference for 3–4 month and 5–6 month refills respectively. More than 65% encountered barriers to receiving their ARVs and about 25% defaulted while abroad [14].

Previous lessons have been learnt to allow for improved management of risk when implementation multi month dispensing ART projects. We anticipate this will include a need for reliable supply of medication [15], access to quality clinical data and linkages, including VLs results, frameworks to support lay worker’s cadre [16, 17], involvement of community stakeholders, and reliable data systems and records of key indicators. The design to be used namely a pragmatic, parallel, cluster-randomized non-inferiority design has the following advantages that add rigor to findings [18]. Additionally, the non-inferiority design aims to determine whether a new approach is not worse than a standard approach by more than a preset margin [19].

In Lesotho, viral load monitoring is performed annually for stable adult’s patients on ART. We anticipate missing viral results. Viral load suppression is thus a secondary outcome. Our findings will be interpreted with care when generalizing to other settings, as there are varying definitions of the term stable patients [20], which is an inclusion criterion in the current study. Additionally, we will not ascertain outcomes of unstable ART patients that will be screened out who may have potentially benefited from the interventions. Large quantities of drugs will be supplied to those that will enroll in the 3 and 6-month arms (including ART, CPT and IPT). This will be challenging for patients who have not disclosed their HIV status to family members leading to erroneous disclosure of HIV status. There is risk for patients to share medication with peers. Both participants and providers will not be blinded, and this might lead to participants wanting to transfer to another arm. Regardless of arm, participants are more likely to be retained if they are aware they are part of a study.

Despite these limitations, this study has a robust design, it is will be the first randomized study to explore the outcomes of retention, virologic suppression and cost effectiveness through differentiated community ART distribution approaches in Lesotho. The study will provide important data regarding the effectiveness of community models for ART distribution and is anticipated to inform policy regarding best practice among HIV-positive patients receiving ART and what is needed to strengthen health systems for rapid scaling up of ART in a contextualized, sustainable and cost-effective manner.

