**Methods:**

This study will be a three-arm cluster randomised trial, which will enrol approximately 5760 HIV-infected individuals who are stable on ART in 30 selected clusters. The clusters, which are health facilities, will be randomly assigned into the following differentiated model of care arms: (i) 3 monthly ART supply at facilities (Control), (ii) 3 monthly ART supply through community ART groups (CAGs) and (iii) 6 monthly ART supply through community ART distribution points (CAD). Primary outcomes are retention in care and virologic suppression, and secondary outcomes include feasibility and cost effectiveness.

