Potential benefits for this approach includes (i) higher adherence to ART and retention in care, (ii) reduced per-patient cost of providing ART, by reducing the number of clinic visits required, (iii) decongestion of clinics to allow for increased capacity to manage patients newly diagnosed with HIV, those with infectious complications, treatment failure, and other co-morbidities and (iv) decreased waiting time and improved efficiency at clinics allowing for improved quality of care and patient satisfaction [7, 8].

Limited data are available from LMICs on multi-month scripting and dispensing and on studies using community-based models of care. A review of the literature reveals a lack of randomized studies of different ART dispensing intervals. An abstract presented at the Conference on Retroviruses and Opportunistic Infections, 2016 using Zambian data, suggested that requirements for monthly dispensing and/or systems that require multiple separate visits for refills and clinician evaluation can raise significant challenges for people living with HIV and result in treatment interruptions or complete disengagement from care [6].

This study’s primary objectives are (i) to determine if stable patients receiving 3 monthly dispensing of ART within CAGs have non-inferior retention in care and viral load suppression than stable ART patients receiving 3 monthly dispensing at health facilities after 12 and 24 months, (ii) 6 monthly dispensing of ART within the community from a health care worker have non-inferior retention in care than stable ART patients receiving 3 monthly dispensing at health facilities after 12 and 24 months and (iii) 6 monthly dispensing of ART within the community from a healthcare worker have non-inferior retention in care than stable ART patients receiving 3 monthly dispensing within CAGs after 12 and 24 months. The secondary objectives are to compare cost outcomes (cost per patient retained and cost per patient retained with viral suppression) between the three models, investigate the acceptability of 3 and 6 monthly community-based ART distribution among patients and service providers and to assess if there are measurable gains in clinic productivity realized following the introduction of community based MMD of ART.

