### Study measures and outcomes (data collection matrix)

The schedule of visits and evaluations to be done are outlined see Additional file 1. The primary outcomes to be compared between arms for this study are retention and VL suppression. Secondary outcomes will include the following (i) comparisons in cost effectiveness between arms, (ii) acceptability of models to patients and service providers and (iii) measurable gains in decongestion in facilities through motion time assessments/analysis.

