### Viral load testing for enrolled patients (at 12 and 24 months)

As the study will be using VL results from routine monitoring as an inclusion criterion, some participants will have a VL test due soon after enrolment into the study. To synchronize patient care and study VL tests, due routine VL tests will be done as scheduled unless the test is due at 2 months before or after the required study-specific VL test at 12 and 24 months for the study, in which case the study-specific VL will be used for patient management. At 12 and 24 months after enrolment in the study, all patients are required to visit the facility for a VL test.

In this study, there will be no active contact with study participants during the period of follow-up. However, when participants are due for the above-mentioned routine, annual VL assessments, study staff will help ensure each site has capacity to collect these samples and will support systems that help to provide results back to sites. VLs will only be performed on individuals who return for visits and no tracing will be performed by the study for obtaining annual VLs. VLs will be considered within the window for the annual visit if they are performed in a window of +/− 90 days.

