### Study end points and definitions

Endpoints will be determined by record reviewing. The primary endpoint will be reached (12 months) and re-assessed after the 24-months. Endpoint data collection will include:(i)Retention in care defined as participant attrition, where attrition is defined as either death (all-cause) or loss to follow-up (LTFU). LTFU will be defined as no facility or ART collection for > 90 days after the last missed scheduled ART collection. Participants with documented transfers to another clinic will be considered retained at the next immediate time point (12 or 24 months), and will then be censored.(ii)Suppressed VL of < 1000 copies/mL done as part of annual VL or performed at any other time during the follow-up, if ordered by clinician due to clinical concern (secondary).

The following will be considered not retained unless otherwise noted:(i)Retained in care but with transitioned off assigned study arm for any reason (patient preference, provider preference, development of ART toxicity requiring switch and closer monitoring and any other complications)(ii)Transferred to another clinic (if a documented transfer, will be considered retained and analysed as such at the next assessment point.(iii)Death.

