### Sample size estimate

Sample sizes were determined for a cluster randomized non-inferiority trial with retention in care at 12 months as the primary outcome. A total of 30 study sites will be available for randomization, with three study arms, 10 clusters per arm, and participant enrolment numbers will be assumed to be equal at each site. The probability of patient attrition 12 months after study enrolment is assumed to be 5%. An intra-cluster correlation coefficient of 0.01 for patient retention/attrition amongst stable ART patients is assumed from a previous cluster randomized trial including stable ART patients [9]. The non-inferiority limit is specified as 3.25%. Assuming α = 0.05, power of 85%, and using a one-sided Z-test (un-pooled) statistic, approximately 192 enrolled participants per facility will be required with a total sample size of 5760 participants, representing 1920 participants per arm.

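### Viral load suppression is primary in three places and secondary in the Discussion, and its primary non-inferiority claim has no margin or power of its own

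*Protocol article*

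**What the plan says.** **VL suppression as primary**
- Abstract, Methods: "Primary outcomes are retention in care and virologic suppression".
- Study measures and outcomes: "The primary outcomes to be compared between arms for this study are retention and VL suppression".
- Background, primary objective (i): patients in community ART groups (3MC) are to "have non-inferior retention in care and viral load suppression than stable ART patients receiving 3 monthly dispensing at health facilities", at 12 and 24 months. Objectives (ii) and (iii), which concern the 6-monthly arm (6MCD), name retention only.

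**VL suppression as secondary, or retention alone as primary**
- Discussion: "Viral load suppression is thus a secondary outcome". The reason given is that missing results are expected.
- Sample size estimate: the trial is sized "with retention in care at 12 months as the primary outcome".
- The recruitment section refers to retention, alone, as the primary study endpoint when it explains the ban on co-enrolment.
- Study end points and definitions: the VL item ends with the bracketed word secondary. It is unclear whether this labels the whole VL endpoint or only the clinician-ordered tests.

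**How VL is obtained**
- Viral load testing section: "VLs will only be performed on individuals who return for visits and no tracing will be performed by the study for obtaining annual VLs". The annual test has a window of ±90 days.
- Study end points and definitions also admits tests "performed at any other time during the follow-up, if ordered by clinician due to clinical concern".

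**The concern.** The hierarchy of outcomes decides what counts as success. A reader of the Abstract, objective (i) or the outcomes section would expect the trial to conclude on VL suppression as well as on retention. A reader of the Discussion or the sample size section would not. The Discussion itself describes non-inferiority as being not worse by more than a margin set in advance, and no such margin exists for VL.

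Participants and providers are not blinded, and enrolment had been under way since 7 August 2017 when the article appeared. Outcome information can accumulate while either status for VL could still be defended from the text.

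Ascertainment adds to the problem. Returning for a visit happens after randomisation and is closely tied to retention, which the interventions may change. A VL comparison restricted to tested patients would condition on it. Counting clinician-triggered tests at any time also sits uneasily with the fixed window for the annual test.

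**Working it through.** **1. Which outcome the sample size covers.** Inputs from Sample size estimate: attrition 5% in both arms, margin 3.25 points, one-sided α 0.05, power 85%, ICC 0.01, 10 clusters of 192 per arm.

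- Per arm without clustering: (1.645 + 1.036)² × 2 × 0.05 × 0.95 / 0.0325² = 647.
- Design effect: 1 + (192 − 1) × 0.01 = 2.91.
- Per arm with clustering: 647 × 2.91 = 1883, against 1920 stated (1.9% apart).
- Power at 1920 per arm: SE = √(2 × 0.05 × 0.95 × 2.91 / 1920) = 0.0120, and Φ(0.0325/0.0120 − 1.645) = 85.6%, against 85% stated.

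The stated number reproduces as a retention calculation and is not at fault. All its inputs describe retention or attrition.

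**2. What is given for VL suppression.** The article gives no margin, suppression rate, ICC, missing-VL rate or power for it.

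**3. Whether the retention sizing can stand in for VL.** This cannot be settled from the article. The illustration below borrows the retention margin, ICC and α. The suppression and missingness rates are assumptions.

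| Suppression, both arms | Power, no VL missing | Power, 30% of VLs missing |
|---|---|---|
| 98% | 99.5% | 98.9% |
| 95% | 85.6% | 81.2% |
| 90% | 62.7% | 57.7% |
| 85% | 50.3% | 46.0% |

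Example, 90% with none missing: SE = √(2 × 0.10 × 0.90 × 2.91 / 1920) = 0.0165, and Φ(0.0325/0.0165 − 1.645) = 62.7%. The table shows that VL power is undetermined. It does not show that power is too low.

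**4. How return-only testing can mislead.** Assume 95% of tested patients are suppressed in both arms, with 85% tested in one arm and 95% in the other.

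- Among the tested: difference 0.
- All enrolled, untested counted as not suppressed: 0.85 × 0.95 = 80.75% against 0.95 × 0.95 = 90.25%, a difference of −9.5 points.
- All enrolled, untested counted as suppressed: 80.75% + 15% = 95.75% against 90.25% + 5% = 95.25%, a difference of +0.5 points.

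The answer depends on the scoring rule, and the tested-only figure reveals neither extreme.

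**The case against.** **The intended answer is visible.** The sample size section, the recruitment section and the Discussion all point to retention, and the bracketed tag in the endpoint definition may do so too. This stands, and it makes the repair easy. It does not remove the opposite statements in the Abstract, objective (i) and the outcomes section.

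**The analysis plan may deal with it.** A plan that is not shown could set a VL margin, a denominator and a rule for missing results. The absence of the last two from an article is no fault in itself. No plan, however, can make the article's own statements about the status of VL agree.

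Four stronger readings are tempting, and the documents do not support them.

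- *Suppression will be analysed among tested patients only.* The article says who is tested, not who is analysed, and the statistical section specifies intention-to-treat. Tested-only bias is a risk to close off, not a stated analysis.
- *Triggered tests push towards non-inferiority because facility patients are seen more often.* Ill members of community groups are told to report to the clinic. Health workers assess adherence and refer at 6-monthly refills. Unstable participants in the community arms return to facility follow-up. Any of these could raise triggered testing in the community arms, so the direction is open.
- *The trial is underpowered for VL.* The figures above rest on assumed rates and a borrowed margin. A secondary outcome reported as an estimate needs no power.
- *The endpoint definition settles the matter as secondary.* The tag can equally be read as covering only clinician-ordered tests.

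**Conclusion.** Wrong as written. Three places make VL suppression primary, one of them as a non-inferiority objective. The Discussion calls it secondary, the endpoint definition is ambiguous, and two further places treat retention as the primary endpoint. Objective (i) therefore states a primary non-inferiority claim with no margin or power of its own. This conclusion rests on the text alone and needs no assumed rate.

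The consequence is that what the trial may conclude on VL stays open to choice after outcomes are seen. The numerical effect cannot be sized, because the article gives no VL rate, ICC or missingness. Bias from return-only and triggered testing is possible, but its direction is not certain. The retention sample size is unaffected.

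**What to change.** **Give VL one role.** State in the Abstract, the objectives, the outcomes section and the endpoint definitions that 12-month retention is the sole primary outcome. State that VL suppression is secondary at 12 and 24 months for all three comparisons, and remove the VL non-inferiority wording from objective (i). If the sponsor prefers to keep a VL non-inferiority claim, it must state a VL margin, the assumed suppression rate, the ICC and the resulting power.

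**Define the endpoint.** At each time point, use the VL nearest to it within the existing ±90-day window. Report clinician-triggered tests outside the window separately.

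**Report it among all enrolled, with a 95% confidence interval.** State rules for three groups:
- participants with no VL in the window;
- documented transfers, who count as retained at the next time point but may have no VL;
- participants moved off their arm but still in care. Their VL should be used. The retention rule counts them as not retained, and carrying that over would score suppressed patients as failures by arm.

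Give suppression among the tested as supportive only.

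**Cost.** Wording in four places, one derived variable at each time point and three scoring rules, with no change to sample size or visits. The downside is that there is no formal VL non-inferiority claim unless the sponsor sets a margin for one.

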### Trial status

Recruitment and enrolment began 7 August 2017 and is still on going.

## Abbreviations

3MC: 3 monthly ART supply through community ART groups
3MF: 3 monthly ART supply at facilities
6MCD: 6 monthly ART supply through community distribution points
AIDS: Acquired immunodeficiency syndrome
ART: Antiretroviral treatment
CAD: Community ART distribution points
CAGs: Community ART groups
CD4: Cluster of differentiation 4
CPT: Co-trimoxazole
FGD: Focus group discussions
GEE: Generalized estimating eqs.
HIV: Human immunodeficiency virus
IPT: Isoniazid
KII: Key informant interviews
LMICs: Low-middle income countries
LTFU: Lost to follow up
MMD: Multi-month dispensing
PEPFAR: U.S Presidential Emergency Plan for AIDS Relief
PLHIV: People living with HIV
SPIRIT: Standard Protocol Items: Recommendations for Interventional Trials
TB: Tuberculosis
UNAIDS: Joint United Nations Programme on HIV and AIDS
USAID: United States Agency for International Development
VL: Viral load
WHO: World Health Organization
